## Methods and design

This paper was guided by the Consolidated Standards of Reporting Trials (CONSORT) (Fig. 1) and the Standards for Reporting Implementation Studies (StaRI) Checklists (Additional Files 1 & 2).

**Fig. 1 Fig1:**
[figure not shown]
CONSORT flow diagram

### Study design

The RESETTLE-IDPs study employs a cluster-ized type 2 hybrid effectiveness-implementation trial design [44]. This design allows for the simultaneous evaluation of the clinical effectiveness of the LSE intervention on mental health outcomes and the assessment of implementation outcomes to inform potential scale-up and sustainability [45]. The design will also allow the comparison of the in-person and the mobile arm.

The study will be conducted in two phases using a community-partnered participatory approach :

Phase (1) a formative phase to culturally adapt the LSE intervention and engage stakeholders; and.Phase (2) an intervention phase to evaluate the effectiveness and implementation of the LSE program delivered through in-person peer support groups or Mobile -facilitated peer groups.

### Study setting and participants

The study will be conducted in IDP host communities in Maiduguri, the capital of Borno State in Northeast Nigeria. Since the emergence of the Boko Haram conflict in 2009, Maiduguri has become the hub of IDPs and hosts the highest proportion of IDPs in the country, 76%. An estimated 49% of these IDPs reside in 237 camp/camp-like settings, and 51% are in host communities [4]. The IDP host communities will be our unit of randomizing, using a computer generation. Selection criteria for our two study sites include population size, non-existence of MHPSS, network availability, and the presence of local partners and infrastructure to support the research.

The target population includes IDPs 13 years and older who have been displaced for at least three months. Participants will be recruited through a combination of purposive sampling strategies, with the assistance of camp leaders, community mobilizers, and humanitarian organizations in those sites, given the intervention delivery approach: in-person and mobile arm group. Inclusion criteria are: (1) resident in IDP camp for 6 months; (2) aged 18 years or older; (3) speaks English or Hausa; (4) having access to a mobile phone or being willing to share one (for the Mobile, i.e., WhatsApp, arm); and (5) providing informed consent/assent. It is important to note that while device sharing is allowed for participation in the Mobile arm, it may pose potential risks to participants’ privacy and confidentiality. Measures will be taken to mitigate these risks, such as providing guidance on secure device sharing practices and ensuring that shared devices have appropriate security features enabled.

Exclusion criteria include (1) the presence of mental illness, cognitive impairment, or substance abuse that would hinder meaningful participation following the baseline assessment; (2) imminent risk of suicide or violence requiring immediate referral; and (3) unwillingness to participate in the study or complete study assessments.

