**Methods:**

This cluster-randomized hybrid type 2 effectiveness-implementation trial will be conducted in 20 IDP camps or host communities in Maiduguri, Nigeria. Sites will be randomly assigned to receive a 12-week LSE program delivered either through in-person peer support groups or WhatsApp-facilitated mobile groups. The study will recruit 500 participants aged 13 years and older. Intervention effectiveness outcomes include the primary outcome of change in post-traumatic stress disorder (PTSD) symptoms assessed using the PCL-5 scale, and secondary outcomes of depression, anxiety, well-being, and life skills acquisition. Implementation outcomes will be assessed using the Acceptability of Intervention Measure (AIM), Intervention Appropriateness Measure (IAM), and Feasibility of Intervention Measure (FIM). Both sets of outcomes will be compared between the in-person and mobile delivery groups. Quantitative data will be analyzed using mixed-effects linear regression models, while qualitative data will be examined through reflexive thematic analysis. The study will be guided by the Reach-Effectiveness-Adoption-Implementation-Maintenance (RE-AIM) framework.

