### Sample size and power analysis

The target sample size of 500 participants (250 per arm) was calculated based on the primary outcome of change in PTSD symptoms, as measured by the PCL-5. The sample size was determined to detect a minimum effect size (Cohen’s d) of 0.4, which represents a clinically meaningful difference in PTSD symptoms between the two intervention arms. This effect size is consistent with previous studies of psychosocial interventions for conflict-affected populations [46]. The power calculation assumed a two-sided significance level of 0.05, a power of 80%, and an intra cluster correlation coefficient (ICC) of 0.05 to account for the clustering of participants within IDP camps or communities. The ICC was estimated based on previous cluster-randomized trials of mental health interventions in humanitarian settings [47]. To account for potential attrition, the sample size was inflated by 15%, based on an anticipated dropout rate of 10–15% over the 12-week intervention period. This attrition rate is consistent with previous longitudinal studies of IDPs and takes into consideration the potential challenges of retention in the context of ongoing displacement and insecurity [48].

Based on these parameters, a total of 20 clusters (10 per arm) with an average of 25 participants per cluster (500 participants in total) will provide sufficient power to detect a clinically meaningful difference in PTSD symptoms between the in-person and mobile-delivered LSE interventions, while accounting for clustering and attrition.

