### Data analysis

Implementation outcomes will be assessed using the Acceptability of Intervention Measure (AIM), Intervention Appropriateness Measure (IAM), Facilitator Fidelity logs, observation checklist of program implementation and observation of staff training on the life skills curriculum, and Feasibility of Intervention Measure (FIM) [59]. Cost-effectiveness will be calculated by estimating the total program costs and comparing them to the achieved health outcomes.

Qualitative data analysis will employ a reflexive thematic analysis approach using both inductive and deductive coding strategies to identify key themes related to implementation, acceptability, fidelity, and feasibility. Transcripts will be coded iteratively to identify emerging themes and patterns, with constant comparison within and across cases. Memos and matrices will be used to facilitate synthesis and interpretation. Triangulation of qualitative and quantitative findings will be performed to enhance validity and identify convergent and divergent results [60, 61].

Quantitative data analysis will follow an intention-to-treat approach, using mixed-effects linear regression models to assess intervention effects on primary and secondary outcomes. Models will include fixed effects for time, group assignment, and their interaction, and random effects for clusters and participants. Baseline characteristics will be included as covariates to adjust for potential confounding. missing data will be handled using list wise deletion (complete case analysis) or multiple imputation (MI) methods.

Effect sizes will be expressed using Cohen’s (standardized mean differences) with 95% confidence intervals. To account for potential biases from unmeasured confounders, propensity score matching will be employed to adjust the effect size estimates.

intervals. Subgroup analyses will explore differential effects by gender, age, displacement duration, and baseline symptom severity. Sensitivity analyses will be conducted to assess the robustness of the findings to different assumptions and methods.

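### No stratification or constraint is named for allocating 20 clusters that may mix camps and host communities, and the propensity score matching planned for the analysis cannot do what it is said to do

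*Protocol article*

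**What the plan says.** The only description of the allocation method is in Study setting and participants: "The IDP host communities will be our unit of randomizing, using a computer generation". The abstract adds that sites are assigned at random. Neither place mentions strata, pairs, minimisation or constrained randomisation.

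The article is not consistent about what the clusters are:
- The abstract says the trial "will be conducted in 20 IDP camps or host communities in Maiduguri, Nigeria". Sample size and power analysis likewise refers to camps or communities.
- Study setting and participants names host communities only, both as the place of the study and as the unit of randomisation. Its first inclusion criterion nevertheless requires six months' residence in an IDP camp.
- The same section gives background on the displaced population: "An estimated 49% of these IDPs reside in 237 camp/camp-like settings, and 51% are in host communities". It also lists population size among the criteria for choosing two study sites.

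The design is "a total of 20 clusters (10 per arm) with an average of 25 participants per cluster (500 participants in total"), aimed at a Cohen's d "of 0.4, which represents a clinically meaningful difference in PTSD symptoms between the two intervention arms".

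Data analysis specifies intention-to-treat mixed models with a random effect for cluster and baseline characteristics, not named, as covariates. It then states that, because of possible unmeasured confounding, "propensity score matching will be employed to adjust the effect size estimates".

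**The concern.** With 10 clusters per arm, a cluster-level factor can easily fall unevenly between arms. Camp versus host community is an obvious candidate, because living conditions and services may differ between them and the article itself separates the two. A restricted allocation would remove most of that variation at almost no cost, but the article names none.

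The stated analysis does not clearly fill the gap. Setting is not named as a covariate. Propensity scores are built from measured variables, so matching on them cannot deal with unmeasured confounders. At cluster level there are only 10 units per arm to match. Matching may also discard randomised participants, which conflicts with the intention-to-treat approach in the same section.

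At stake are the precision of the primary contrast and its credibility if the arms visibly differ in setting.

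**Working it through.** **Inputs from the article:** 20 clusters, 10 per arm, mean size 25, ICC 0.05, d = 0.4, two-sided 5% level, 80% power, 15% inflation.

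**Assumed, because the article does not give them:** the number of camps among the 20 clusters (central case 10, range 6 to 12), and the camp/host difference δ in PCL-5 change (0.2 to 0.447 SD).

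**1. The article's sample size.** A difference of 0.4 SD needs 99 per arm without clustering. The design effect is 1 + (25 − 1) × 0.05 = 2.2. Then 2 × 99 × 2.2 = 435.6, and 435.6 × 1.15 = 501 (or 435.6 / 0.85 = 512). The stated 500 is reproduced.

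**2. Chance of a camp imbalance.** With 10 camps among 20 clusters and 10 per arm, P(k camps in one arm) = C(10,k)² / C(20,10), where C(20,10) = 184,756.
- 6:4 or worse: 1 − 252²/184,756 = 1 − 63,504/184,756 = 0.656
- 7:3 or worse: 2 × (14,400 + 2,025 + 100 + 1)/184,756 = 0.179
- 8:2 or worse: 2 × (2,025 + 100 + 1)/184,756 = 0.023

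The result depends little on the number of camps. A difference of four or more camps between arms has probability 0.141 with 6 camps and 0.170 with 8 or 12.

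**3. Ceiling on δ.** With half the clusters camps, setting contributes between-cluster variance δ²/4. This cannot exceed the ICC, so δ ≤ √(4 × 0.05) = 0.447 SD.

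**4. Shift in the arm contrast** = (difference in camp share) × δ. In brackets, the share of d = 0.4:

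| Split | δ = 0.2 | δ = 0.3 | δ = 0.447 |
|---|---|---|---|
| 6:4 | 0.04 (10%) | 0.06 (15%) | 0.09 (22%) |
| 7:3 | 0.08 (20%) | 0.12 (30%) | 0.18 (45%) |
| 8:2 | 0.12 (30%) | 0.18 (45%) | 0.27 (67%) |

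The difference in camp share has a standard deviation of 0.229. The typical shift is therefore 0.229δ: 0.05 SD at δ = 0.2 and 0.10 SD at the ceiling (11% and 26% of target).

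**5. Is this already in the standard error?** SE = √(2 × 0.05/10 + 2 × 0.95/250) = √(0.0100 + 0.0076) = 0.133 SD. The between-cluster part is √0.0100 = 0.100 SD. If setting explains the whole ICC, the typical shift in step 4 is 0.10 SD, essentially the same quantity. So the planned analysis already allows for it.

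**6. Gain from balancing on setting and fitting it.** The between-cluster variance falls to 0.05 − δ²/4.
- δ = 0.2: √(2 × 0.0400/10 + 0.0076) = 0.125
- δ = 0.3: √(2 × 0.0275/10 + 0.0076) = 0.1145
- δ = 0.447: √0.0076 = 0.087

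All compare with 0.133 without balance. At 15% loss (21.25 per cluster), power from the noncentral t distribution is 78.5% on 18 df without stratification. With it, on 17 df, power is 82.5% at δ = 0.2 and 88.0% at δ = 0.3.

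**7. Adjustment without balance.** At a 7:3 split, fitting setting as a covariate removes the shift but inflates the variance by 1/(1 − 0.4²) = 1.19. At δ = 0.3 the SE is then 0.1145 × √1.19 = 0.125, between the unadjusted 0.133 and the balanced 0.1145.

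**The case against.** **The article does not say that allocation is unrestricted.** A reader might infer simple randomisation from the one sentence on method. A stratified or constrained sequence is also computer generated, the fixed 10 per arm shows that arm size at least is controlled, and a journal article may leave strata to the full protocol. This objection stands, so the probabilities above apply only if no restriction is used.

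**The mix of clusters is uncertain.** The 49% and 51% figures describe where displaced people live, not the trial's clusters. If all 20 are of one type, there is no camp/host imbalance. Population size is given as a criterion for choosing two study sites, not as a feature of the 20 randomised clusters. This also stands, and it means that the inconsistency must be resolved first.

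**Chance imbalance is not bias.** A reader might infer that an uneven split would produce a false treatment effect. Under random allocation the shift is equally likely in either direction (about 9% each way for 7:3 or worse). The ICC and the cluster random effect already allow for it, as step 5 shows. The test remains valid.

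**Adjustment can work.** The planned covariates could include setting, and that would remove a measured imbalance. The outcome is also change from baseline, so stable differences in level cancel. Both points stand. What remains is that setting is not named, and that adjustment after an uneven split is less efficient than balance by design (step 7).

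**The article does not tie the matching to cluster imbalance, or state its level.** That is correct. But the purpose it does state, unmeasured confounding, is one that matching cannot serve at either level.

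**Conclusion.** The point holds as a design improvement with a modest, conditional size. The article names no restriction on allocating 20 clusters that it elsewhere describes as mixed, and it includes a matching step whose rationale is wrong as written.

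If about half the clusters are camps and allocation is unrestricted within 10 per arm, a 7:3 or worse split has an 18% chance. Such a 7:3 split shifts the contrast by 0.08 to 0.18 SD, or 20% to 45% of d = 0.4. This rests on an assumed setting effect of 0.2 to 0.45 SD and on the article's ICC of 0.05. The cost is precision and face validity.

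The figures do not support a claim that imbalance could readily account for half the target effect or more. At 7:3, half the target needs δ = 0.5 × 0.4/0.4 = 0.5 SD, above the 0.447 SD ceiling. An 8:2 or worse split has only a 2.3% chance. The sample size of 500 is not in question.

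**What to change.** 1. Reconcile the abstract, Study setting and participants, and Sample size and power analysis on whether clusters are camps, host communities or both.
2. If they are mixed and not yet allocated, randomise within camp and host strata, or use constrained randomisation on setting and cluster population size. If all are of one type, constrain on population size only. If a restriction is already in place, state it.
3. Name the stratum as a fixed effect in the primary mixed model. If allocation has already taken place without strata, still prespecify setting as a covariate.
4. Delete the propensity score matching and rely on prespecified covariate adjustment.

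The cost is an allocation script, one model term and one degree of freedom (18 to 17). The sample size stays at 500. With stratification and an even number of camps, the camp-share difference is zero. With an odd number it is at most one cluster, a shift of at most 0.10 × 0.447 = 0.045 SD (11% of target) before adjustment.

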**Fig. 2 Fig2:**
[figure not shown]
The life skills education scope

In the in-person arm, participants will attend weekly 120-minute peer support group sessions facilitated by trained IDP men and women and supervised by local mental health workers. The groups will be gender- and age-segregated (13–15, 16–19, and 18 + years) to create safe spaces for open discussion and skills practice. Sessions will employ interactive and experiential learning techniques such as role-plays, storytelling, games, and art-based activities to enhance engagement and retention.

In the mobile arm (i.e. WhatsApp), participants will join gender- and age-specific mobile groups moderated by trained facilitators. The groups will receive weekly LSE content and exercises through a combination of messages, voice notes, images, and live audio sessions. Participants will be encouraged to share reflections, ask questions, and provide peer support through the WhatsApp chat. Facilitators will stimulate discussion, offer feedback, and monitor participant safety and engagement.

Both arms will receive the LSE intervention for a duration of 12 weeks, with an average of 10–12 participants per peer support group. Fidelity to the intervention will be assessed through structured observations, attendance records, and facilitator logs [52]. Participants will receive the equivalent of $20 US and be provided with snacks during the intervention. Participants will also have access to referral information for additional mental health and social services as needed.

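### The inclusion criteria contradict the rest of the protocol on age (18+ against 13+) and on setting (camp residence against randomised host communities), and two age bands overlap

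*Protocol article*

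**What the plan says.** **Age.** The abstract says "The study will recruit 500 participants aged 13 years and older". Under Study setting and participants, "The target population includes IDPs 13 years and older who have been displaced for at least three months". The inclusion list in that same paragraph begins "Inclusion criteria are: (1) resident in IDP camp for 6 months; (2) aged 18 years or older", and its fifth criterion is "providing informed consent/assent". Under The adapted evidence-based intervention, in-person groups are "gender- and age-segregated (13–15, 16–19, and 18 + years".

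**Setting and duration.** Study setting and participants states "The study will be conducted in IDP host communities in Maiduguri" and "The IDP host communities will be our unit of randomizing". It separates the two settings, putting an estimated 49% of these displaced people in camps or camp-like settings and 51% in host communities. The abstract allows either setting for the 20 sites, and the sample size section speaks of camps or communities. The first inclusion criterion names only camps and asks for six months of residence. The target population is defined by three months of displacement.

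**Groups.** Both arms run for 12 weeks "with an average of 10–12 participants per peer support group". The mobile groups are also separated by gender and age, but no bands are given for them. The sample size section plans 20 clusters with an average of 25 participants each.

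**The concern.** Eligibility defines the population to which the primary PCL-5 comparison applies. Here one paragraph gives two age rules and two settings. Field staff who follow the inclusion list would turn away every minor; staff who follow the target population, the assent provision and the group plan would enrol them. If sites read the text differently, the age mix would differ between clusters for reasons unrelated to allocation, and analysis cannot restore people who were never enrolled. The age rule also decides whether the planned subgroup analysis by age includes any adolescents, and whether assent procedures are needed at all.

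The setting conflict is of the same kind. A criterion that residents of the randomised units cannot meet will be either ignored or applied unevenly. The band overlap is smaller, but it leaves group assignment at ages 18 and 19 to local judgement.

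**Working it through.** **1. Age, places side by side.**

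| Place | Rule or implication |
|---|---|
| Abstract, Methods | 13 and older |
| Target population | 13 and older |
| Inclusion criterion 5 | Consent or assent, which implies minors |
| In-person groups | Bands 13–15, 16–19, 18+ |
| Inclusion criterion 2 | 18 and older |

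Applying criterion 2 to the bands: of ages 13, 14 and 15, none is eligible. Of ages 16, 17, 18 and 19, only 18 and 19 are.

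**2. Band overlap.** The bands 16–19 and 18+ share ages 18 and 19. Under criterion 2 those are the only eligible ages in the 16–19 band, so every eligible member of that band also qualifies for the 18+ band.

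**3. Setting.** The units randomised are host communities; the residence required is in a camp. The protocol counts these as separate settings (49% and 51%). Read literally, a host-community resident fails criterion 1. If the abstract's wider wording governs, camp clusters are unaffected and host-community clusters still have no eligible residents.

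**4. Duration.** Time displaced (at least three months) and time resident in a camp (six months) are different quantities. Someone resident in an IDP camp for six months also meets the three-month rule, so the two can hold together. The people lost are those displaced for three to under six months: they are in the target population but cannot yet have six months in a camp.

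**5. Group size against cluster size.** First, does 25 per cluster follow from the protocol's own inputs (d = 0.4, two-sided α = 0.05, power 80%, ICC 0.05, 15% inflation)?

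- Per arm, unclustered: 2 × (1.96 + 0.84)² / 0.4² = 98 to 99, depending on rounding; 99 is used.
- Design effect: 1 + (25 − 1) × 0.05 = 2.2, so 99 × 2.2 = 217.8 per arm.
- Attrition: 217.8 × 1.15 gives 251 per arm (502 in total); 217.8 / 0.85 gives 257 per arm (514 in total).

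Both are within 3% of the planned 500, so 500 / 20 = 25 per cluster is a sound figure to test against.

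- Groups that 25 people fill: 25 / 12 = 2.1 to 25 / 10 = 2.5, so about two.
- Strata under the stated in-person plan: 2 genders × 3 bands = 6.
- If one cluster ran all six: 25 / 6 = 4.2 people per group, against 10–12.

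Not every stratum can therefore run at the stated size in every cluster if the bands from age 13 are kept.

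**The case against.** The other side has several fair points.

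- **Duration.** Inclusion criteria may narrow a target population, and three months displaced with six months in a camp is not a contradiction. This stands; what remains is a mismatch that needs aligning.
- **Setting.** The abstract and the sample size section cover both settings, and recruitment uses camp leaders, so criterion 1 may be loose wording. That makes the repair small. It does not remove the conflict, because the same section separates camps from host communities and names the latter as the randomised unit.
- **Group size.** A reader might infer that the groups cannot be filled, and scale six groups per cluster up to a shortfall for the whole trial. The document does not support this. It nowhere says that every cluster runs all six strata, and it gives the three bands only for the in-person arm. Two strata per cluster would work. The number of groups per cluster is unspecified, not impossible.
- **Intended age rule.** A reader might infer from the group size that an adults-only design was meant. Any two strata of 10–12 fit a cluster of 25, adolescent ones included, so group size does not show which age rule was intended.
- **Merging across clusters.** A reader might expect mobile groups to be pooled across clusters, breaking independence in one arm. No text describes pooling, and the Discussion plans geographically distinct clusters.
- **Subgroup loss.** No age distribution and no subgroup cut-points are given, so the share of participants lost under an 18+ rule cannot be stated.

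None of this touches the age contradiction or the band overlap.

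**Conclusion.** The point holds for age, setting and band overlap. These are errors in the current text, not details that an article would leave to a fuller document, because the article states the conflicting rules itself.

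The size is categorical. Followed literally, criterion 2 admits no one aged 13–17, and criterion 1 admits no host-community resident although host communities are the named units of randomisation. The number of people affected cannot be derived. The nearest figure is the protocol's own estimate that 51% live in host communities, which describes the source population and not the sample.

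The duration mismatch is lesser. The group arithmetic is secondary and conditional: it assumes 25 per cluster, 10–12 per group, and that the bands from age 13 are kept. Which age or residence rule was intended is for the sponsor to settle; this review does not decide it.

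**What to change.** Before enrolment:

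1. Choose one age criterion and state it identically in the abstract, the target population and the inclusion list. Make the assent provision and the age bands agree with it.
2. Choose one setting and residence criterion that residents of the randomised units can meet, and use the same term for the setting, the unit of randomisation and criterion 1.
3. Align the target population with the duration criterion, saying whether the clock is time displaced or time resident.
4. Make the age bands non-overlapping.
5. As a secondary item, state which gender-by-age groups each cluster runs, given room for about two, and that groups stay within clusters. The power calculation and the cluster random effect both take the cluster as the unit of dependence, so this is worth one sentence.

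The cost is amendment wording, with the consent and assent documents matched to the chosen age rule. No change to the sample size follows from this point. If the bands from age 13 are kept, the price is that not every gender-by-age stratum will be present in every cluster.
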